## Discussion

MM affects 13% of the general population, and its incidence increases with age (59, 60). MM is associated with a lower quality of life, changes in the likelihood of hospital admission, depression, frailty, functional impairment, and polypharmacy (61–63). Several studies have attempted to measure the severity of MM and its relationship to mortality (6–9, 29). However, most of the research that sought to estimate the risk of death in MM patients by using multiple comorbidity indexes indicated a high risk of bias (29).

To date, neither of the MM patterns nor the measure of MM through several mortality indexes have been able to provide an accurate estimate of the severity of MM and the associated risk of adverse health outcomes.

In the era of *omics* and *network medicine*, therefore, characterizing the MM phenotype through the integration of several omics profiles to clinical and functional status could increase knowledge on the pathways involved in MM, thus improving the management of patients and reducing the burden of chronic diseases on healthcare systems.

The molecular signature of patients with MM, along with a 10-year functional and clinical profile that includes drug prescriptions and hospitalizations, will enable us to identify surrogate biomarkers of these features that could potentially be implemented in a clinical setting to identify preventive care strategies and personalized treatments.

Our study seeks to improve the prognostic value of MM in terms of mortality and functional decline throughout a 10-year follow-up period. Moreover, the project strives to characterize MM patterns and assess their relationship with functional impairment. To date, no studies have examined the wide spectrum of relationships between MM patterns, health outcomes, polypharmacy, and several biomarkers associated with healthspan over a 10-year time frame. MM patients are more susceptible to increased risk of disability and hospitalization; therefore, they are not included in clinical trials specifically incorporating biomarkers and functional status.

The availability of a comprehensive longitudinal database in synergy with new biomarkers will also allow us to evaluate how and which inappropriate drug decision-making could lead to the onset of new comorbidities or to functional impairment. Disentangling the relationship between polypharmacy and associated disease outcomes could prevent the onset of new chronic conditions and their relative costs for the National Health System, as well as improve the quality of life of older adults. Providing precise, personalized care is the cornerstone of health services designed for MM patients.

We also aim to construct an accurate, multicomponent algorithm that is inclusive of clinical, functional, and molecular data, capable of predicting at an early stage the onset of new comorbidities, death, and functional decline within 10 years of follow-up. Once validated, this tool could be made available to primary care practitioners for the screening, early diagnosis, and treatment of MM patients, thereby decreasing risks to individuals.

Our study's longitudinal design will also enable us to evaluate the quality of care provided to MM patients and to develop new multidisciplinary personalized care plans based on their clinical, functional, and biological profile. On the basis of the projected risk of adverse health outcomes, tailored, coordinated, and integrated treatment and long-term follow-up strategies will be formulated for each patient. This study will support an integrated health system built around systems medicine and strategic partnerships to manage MM. It could include: (i) an understanding of the social, economic, environmental, epigenetic determinants, molecular, and cellular mechanisms underlying MM; (ii) primary care and practice-based interprofessional collaboration; (iii) carefully phenotyped patients; (iv) the development of unbiased and accurate biomarkers for multiple morbidities, severity, and follow-up of patients; (v) socioeconomic science; (vi) development of guidelines; (vii) training; and (viii) policy decisions.

This approach is expected to improve the implementation of involved personalized medicine in clinical practice to reduce unfavorable outcomes and the deterioration of health conditions in the older population, improve access to healthcare services, and consequently, reduce healthcare expenditure.

The findings of this study are expected to facilitate the transition from conventional medicine into the era of network medicine, where pathway-informed molecular diagnostics will enable the selection of therapy in accordance with the paradigm of precision medicine.

The transition from healthcare provision to personalized medicine requires making new knowledge accessible, placing a greater emphasis on patient perspectives, recognizing the value of molecular pathways in guiding care, building new infrastructure and information management processes, and reshaping healthcare delivery to ensure access to personalized medicine technologies and services (64).

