The PROMOTERA study aims to identify promising biomarkers of healthspan and mortality, such as selected circulating proteins and several DNA methylation biomarkers in the plasma and blood samples of hospitalized older patients recruited by the Reportage project (Trial registration number: NCT01397682; July 19, 2011). The Reportage project is (50) an ongoing prospective observational study involving older patients consecutively admitted to acute care wards in INRCA research hospitals located in the Italian cities of Ancona, Fermo, Cosenza, and Casatenovo. The project began in September 2011 with the aim of creating a large data repository on demographics, comprehensive geriatric assessments, clinical and diagnostic information, and molecular and biological data on older adults receiving acute care. This study included patients who were recruited until 2019. Potential participants were screened for eligibility after they were provided with information describing the study. Eligibility criteria included: age ≥ 65 years, admission to one of the INRCA research hospitals, and written informed consent. In the case of a participant's cognitive decline or impaired judgment, a proxy (relative or caregiver) was requested to give their additional consent. The absence of informed consent from the patient or caregiver (50) resulted in the participant's exclusion from the study. Baseline data were collected for each patient within the first 24 h of hospital admission. Baseline data were incorporated into a minimum data set comprising demographic information, multidimensional geriatric assessment data, clinical, biological, and diagnostic information routinely collected during hospitalization, also utilizing the interRAI Acute Care Instrument (51). Moreover, the Reportage dataset contained information on drug intake (prior to admission, during hospitalization, and at discharge) and diagnostic and treatment procedures performed during hospitalization (including information from X-rays, computerized tomography, ultrasounds, electrocardiograms, magnetic resonance imaging, etc.). The multidimensional geriatric assessment was repeated within 24 h prior to discharge. Blood samples were taken within 24 h of admission and stored at −80°C. A separate and detailed data sheet was used to collect data regarding *ad hoc* investigations to identify biological markers.

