### Phase I: Follow-up update

Follow-up information on the date of death will be provided for all Reportage project patients for up to 10 years.

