### Phase VI: Association of overall biomarkers with primary and secondary outcomes

All the biomarkers validated in stage 2 will be integrated with the clinical, functional and biological data. Several biostatistical and bioinformatics analyses will be conducted to identify biomarker signatures that are strongly associated with primary and secondary outcomes.

The synergy between (a) detailed information about diagnoses for each individual patient, (b) a Comprehensive Geriatric Assessment (CGA), (c) routine laboratory data, (d) epigenetics data, and (e) plasma protein determination will improve the characterization of patients with MM, including the prognostic value for multiple outcomes such as overall mortality, re-hospitalization, and functional decline.

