#### CGA

CGA was conducted at admission and discharge using the validated interRAI Minimum Dataset for Acute Care (MDS-AC) (51), encompassing identification information, demographic data, functional state assessment, number and type of diagnoses, and number and type of medications, treatments, and procedures (50). Functional status was evaluated on the basis of several dimensions: the number of impaired basic and instrumental activities of daily living (BADL and IADL) (48, 52, 53) as a measure of functional status; the cognitive performance scale (CPS) as a measure of cognitive function; sensory functioning (hearing and vision); history of falls; pressure sores and skin conditions; pain; delirium, and behavioral changes; nutritional status and oral health; urinary incontinence; and, recent weight loss.

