#### Use of healthcare resources

Information regarding hospital admissions (number and duration of hospital stays), additional laboratory tests performed, and the use of care services (e.g., nurse home visits, physiotherapy, home help, social transport, and day care facility) were also collected. Up to 10 years of information on the use of healthcare resources will be obtained from the Marche Region's administrative database.

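### Entry requires functional status to 10 years and the Discussion promises prediction of functional decline over 10 years, but function is described only at admission and discharge

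*Protocol article*

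**What the plan says.** **What is promised.** The Discussion says the study seeks to "improve the prognostic value of MM in terms of mortality and functional decline throughout a 10-year follow-up period", and describes a multicomponent algorithm "capable of predicting at an early stage the onset of new comorbidities, death, and functional decline within 10 years of follow-up". It also speaks of a functional and clinical profile spanning 10 years. Strengths and limitations lists, as a strength, the accuracy of functional data gathered over 10 years of monitoring.

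**What is required for entry.** The last inclusion criterion in Phase II: Patient selection asks for information from baseline to 10 years and names functional status alongside death, hospitalization, clinical records, laboratory values, new comorbidities and drug intake.

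**What is measured.** Under Outcome variables, the CGA entry says "CGA was conducted at admission and discharge". Study design agrees: "The multidimensional geriatric assessment was repeated within 24 h prior to discharge".

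**What is collected up to 10 years.** Phase I: "Follow-up information on the date of death will be provided for all Reportage project patients". Study design describes the update as one of survival status. The Overall mortality entry takes survival status from the Marche Region's administrative database. The Use of healthcare resources entry does likewise: "information on the use of healthcare resources will be obtained from the Marche Region's administrative database".

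**The concern.** A prediction model needs an outcome that is measured, on a known schedule, in the patients for whom the model is meant. The article promises a 10-year functional outcome and selects patients on having 10-year functional data, yet it describes no functional assessment after the index discharge.

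Two things are at stake.

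- **Selection.** An entry criterion that depends on function recorded after baseline picks patients by what happened to them later: whether they lived long enough to be assessed again, and whether anyone assessed them. Such a criterion applies to the whole sample of 1,070, including the mortality analysis.
- **The functional model.** If post-discharge scores exist for only some patients, decline would be modelled in that subset while death removes many others from view. The Discussion intends the tool for primary care practitioners, so a model built on a selected subset would be applied to a wider population.

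**Working it through.** The plan states no figure on this point, so the check sets the sections side by side.

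| Outcome | Measurement described | Source described for up to 10 years |
|---|---|---|
| Mortality | Date, place and, when available, cause of death | Marche Region administrative database (Overall mortality); date of death (Phase I) |
| Healthcare use | Admissions, laboratory tests, care services | Marche Region administrative database (Use of healthcare resources) |
| Function (BADL, IADL, CPS) | CGA at admission and within 24 h before discharge (CGA; Study design) | None stated |

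1. Two of the three entries under Outcome variables carry an explicit 10-year source. The functional entry carries none, and its timing is that of the index stay.

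2. The sections that mention long-term function do not fill the gap. Phase II requires it without an instrument, visit or source. The Discussion's 10-year profile is illustrated with prescriptions and hospitalizations, neither of which is a functional measurement. Strengths and limitations asserts such data without saying where they come from.

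3. Not every mention of functional decline is affected. Phase VI refers to "prognostic value for multiple outcomes such as overall mortality, re-hospitalization, and functional decline" with no time horizon, so change from admission to discharge would satisfy it. The same holds for the mention of functional-decline risk in Strengths and limitations. The 10-year horizon is attached to functional decline in two places, both in the Discussion; Strengths and limitations attaches it to functional data.

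4. Death would compete heavily with any long-term functional outcome, on the plan's own inputs. Sample size gives a median survival of 6.2 years in the reference group and a hazard ratio of 1.23.
   - Reference group: 50% dead at 6.2 years, by definition of the median.
   - Raised Δage, assuming proportional hazards and reading 1.23 as the higher hazard: survival at 6.2 years = 0.5^1.23 = 0.426, so about 57% dead.

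   More than half of the first group, and more than 57% of the second, would therefore be dead before year 10. This shows why death must be handled as a competing event and why entry should not hinge on later assessment. It does not measure how many patients lack functional data.

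**The case against.** The strongest case on the other side has four parts.

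**The article says the data exist.** Phase II, the Discussion and Strengths and limitations all assert functional information over 10 years. The CGA entry does not say that function was assessed at no other time, and the Marche database is not said to be the only long-term source. Reportage is an ongoing prospective study with its own published protocol, which is not shown, and the Phase II list implies some clinical information after the first discharge. This stands. A reader might infer that the 10-year functional outcome does not exist; the article does not support that.

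Condensation does not remove the point, however. The article does more than leave out detail: it states when function was assessed and what the long-term data cover, then promises and requires something those statements do not supply.

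**The route of later scores is unknown.** A reader might infer that later scores could come only from patients readmitted to the same hospitals. No section says so.

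**Survivor counts are beside the point.** A reader might work out 10-year mortality as 1 − exp(−ln 2 × 10/6.2) = 67.3% and 1 − exp(−1.23 × ln 2 × 10/6.2) = 74.7%, mean 71.0%, and conclude that function could be known in at most about 1,070 × 0.29 = 310 patients. That needs exponential survival and an equal split, neither of which is stated. It also counts survivors at year 10, whereas the promise concerns decline within 10 years, which patients who later die can contribute to.

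**The consequence is limited.** The primary objective and sample size concern mortality, no secondary objective names 10-year functional decline, and Statistical analysis specifies no model for it. This stands as a limit on severity, but the entry criterion belongs to the methods and affects every analysis.

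**Conclusion.** The point holds as an internal inconsistency. The article requires functional status to 10 years and promises prediction of functional decline over 10 years, while the only functional assessments it describes lie within the index stay and the 10-year data it describes are survival and healthcare use. These sections do not support a 10-year functional-decline outcome as written.

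Its numerical size cannot be given, because the article does not report how many patients have functional scores after discharge. The reach is one advertised outcome plus one entry criterion that governs all 1,070 patients. The conclusion rests on the article's text alone: a full protocol naming a post-discharge source, instrument and schedule for all patients would settle the outcome, though not the problem of selecting patients on data recorded after baseline. It should be corrected before patients are selected.

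**What to change.** 1. In Phase II: Patient selection, remove functional status from the information that must be available to 10 years, so that entry does not depend on later assessment or survival.
2. Identify the source, instrument and timing of post-discharge function, covering all patients. If that cannot be done, define the functional outcome as change in BADL and CPS from admission to discharge, drop the 10-year functional-decline claims from the Discussion, and drop the 10-year functional-data claim from Strengths and limitations. Phase VI needs no deletion.
3. If a long-term proxy is wanted, use the care services listed under Use of healthcare resources, such as nurse home visits or home help, after confirming that the administrative data hold them. Label the result as service use and treat death as a competing event.

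The cost is wording and one narrower advertised outcome. Items 1 and 2 need no new data; item 3 depends on what the administrative database contains.

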## Strengths and limitations

This study will be able to rely on a comprehensive database containing clinical, functional, and biological information on more than 1,000 MM patients who have been monitored for 10 years. This project will highlight the most significant diagnostic and prognostic clinical, functional, and biological markers of MM, thereby recommending their implementation in clinical settings to identify those patients with a higher risk of death, hospitalization, or functional decline. Moreover, this study will enable the identification of those drug interactions that affect older adults. In parallel with patient involvement and empowerment, this study seeks to contribute to improvements in healthcare policies and their implementation in practice.

This study's additional strengths include: (i) the sample cohort composed of hospitalized patients over 65 years of age. For this reason, we expected to find higher mortality rates than those observed in a community-dwelling population. This should significantly reduce the number of censored observations and, consequently, the required sample size to detect these potential modifiers; (ii) the relatively long follow-up period that will allow us to adjust for several confounders and mitigate several sources of bias; (iii) clinical, functional, biological, and mortality data accuracy acquired over 10 years of monitoring; and iv) a dimensionality reduction approach that will be performed to decrease the number of variables by clustering patients into a few groups based on the MM pattern (i.e., cancer, cardiovascular, and neurological) or the functional status.

One limitation of the study is that the sample size could be smaller than required to detect weak associations between the measured biomarkers and potential modifiers of the association between epigenetic age acceleration and mortality risk during the follow-up period. The sample size was designed on the basis of the primary objective of discovering significant associations between epigenetic clocks' Δage and mortality during the 10-year follow-up period. However, due to the number of potential tested modifiers, the Bonferroni correction for multiple comparisons will be applied to prevent false-positive findings. This study will recommend introducing several biomarkers in clinical settings to improve the prognostic value of MM. However, this translational protocol necessitates several estimation and validation phases. A limitation of the project could be the feasibility of a wide-scale implementation of these biomarkers in clinical practice. Nonetheless, the involvement of the most important stakeholders and companies would make it possible to develop new diagnostic and prognostic experimental procedures.

The absence of information regarding the causes of death of patients who died outside of hospital may also be considered to be another limitation of the study. For this reason, the association analysis on causes of death will only be utilized for descriptive purposes and will not be used in the main analyses in order to eliminate their potential influence on the outcomes.

## Ethics statement

The studies involving human participants were reviewed and approved by Ethical Committee of the Italian National Research Center on Aging (CE INRCA 20031, 04/02/2021). The patients/participants provided their written informed consent to participate in this study.

## Abbreviations

MM: multimorbidity
CGA: comprehensive geriatric assessment
hsCRP: C Reactive Protein
IL6: Interleukin 6
DHEA: Dehydroepiandrosterone sulfate
A2M: Alpha-2-Macroglobulin
sRAGE: Soluble receptor for advanced glycation end product
Cyst-C: cystatin C
ADL: activity daily living
CKD: chronic kidney disease
COPD: chronic obstructive pulmonary disease
BMI: body mass index
ATC: Anatomical and Therapeutical Chemical classification system.
